### Sample and eligibility criteria

3.2

RNs, the nursing director, nursing records and patients will be included in this intervention study.

#### Registered nurses

3.2.1

All RNs of the six included wards will be recruited (*N = *92) for attitude measurements. Using stratified convenience sampling, a third (*N = *34) of the RNs will participate as experimental group in GCR training (*N = *17) or as control group (*N = *17). Both groups should contain a similar grade‐skill mix of ward managers, nurse instructors, Advanced Nursing Process mentors and regular RNs. All ward managers will be included. The aim is to empower them for taking responsibility on the Advanced Nursing Process. As role models, their knowledge, attitude and behaviour should spread to their teams. The inclusion criteria are being in a leadership, teaching or clinical position, applying the Advanced Nursing Process and understanding the main national language.

#### Nursing records

3.2.2

By using a web‐based random generator, a sample of nursing records (*N = *180) will be drawn (https://www.random.org/). Nursing records covering at least 4 days and at least one nursing diagnosis will be selected from all six wards (experimental group *N = *90, control group *N = *90). The sample‐size calculation was performed using *t*‐tests for unpaired samples (one‐sided) and bases on previous results for using the Q‐DIO for all three sub‐concepts of the instrument (nursing diagnoses, interventions and outcomes) (Müller‐Staub, Needham, et al., 2008). An effect size of 0.5 (mean) on a scale from 0–4 is assumed. For nursing diagnoses, 32 nursing records per group are required; we assumed an effect size of 0.63 (power 80%). For nursing interventions, 45 records (effect size, 0.53; power, 80%) are required and for nursing outcomes, 44 records (effect size, 0.47; power, 70%) are required. To ensure an even distribution in the experimental and control groups, 15 nursing records will be selected per ward (*N = *45 records before and 45 records after the study intervention, totalling *N = *90) for each group (Bortz & Schuster, 2016).

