#### Patients

3.2.3

From the randomly selected nursing records, four patients per ward will be included (*N = *24) to participate in interviews and clinical observations. The inclusion criteria are patients older than 18 years, physically and mentally capable to take part in the interview (e.g. without serious symptoms and completely oriented) and being able to answer interview questions in the main national language.

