### Expected outcomes

3.4

The primary outcomes are the level of the nurses’ knowledge, the level of their attitude, satisfaction with GCR, the quality of nursing diagnoses, interventions and outcomes and the frequency and variety of NANDA‐I‐nursing diagnoses (Doenges et al., 2014; NANDA‐I, 2016). The secondary outcomes are nurses’ behaviour in the field of work (clinical performance of the Advanced Nursing Process evaluated by observations and by patient interviews) and mutual comparisons of all findings.

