##### Tool for demographic and organizational data

3.5.1.7

To control for influencing factors, all participating nurses will be asked about their gender, highest education grade, years of practical experience and previous seminars on the nursing process. To control for system influences, the number of beds, capacity, patients’ length of stay, nurse–patient ratio, grade and skill mix, staff turnover and organizational system characteristics will be collected from each ward by the principal investigator using standardized data collection forms.

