### Data analyses

3.6

The knowledge test and nurses’ attitude (PND scale) will be analysed using descriptive and inductive statistics. Single‐item and total scores will be compared between the two measurement points (Wilcoxon signed‐rank test) and between the experimental and control groups (Mann–Whitney *U* tests). The scores of supplementary control items for the knowledge test will be separately analysed and compared between the two measurement points and the two groups. The results of the three nurses’ attitude measurements (*t*0_2_, *t*1 and *t*2) will be evaluated using Friedman tests (Bortz & Schuster, 2016; Clauß, Finze, & Partzsch, 2011). The free‐text item answers in the knowledge test will be analysed using Mayring's (2010) seven‐step content analyses.

Participant satisfaction will be descriptively analysed based on absolute and relative frequencies and distributions. Content analyses (Mayring, 2010) will be applied to the interview with the nursing director and to the free‐text data from the satisfaction surveys.

The Q‐DIO R scores will be summed for each sub‐concept. If the data are normally distributed, unpaired *t*‐tests are applied to compare pre‐ and postintervention scores and to compare the experimental and control groups. The frequencies and patterns (variety) of the NANDA‐I nursing diagnoses will be compared between the two measurement time points and between the experimental and control groups.

Correlations among nurses’ knowledge, attitude, Q‐DIO R scores, demographic and organizational characteristics will be analysed depending on level of data and testing requirements by Pearson product–moment correlations, Spearman correlations or chi‐squared tests. All tests will be evaluated one‐sided (levels of significance 0.05) using IBM SPSS Statistics 24 (SPSS Inc.).

The qualitative evaluation of nurses’ clinical behaviour will be performed by within‐ and cross‐case analyses (Kuckartz, 2016). Qualitative observations, interviews and nursing records will be analysed using the first and second coding cycles (Saldaña, 2015). Decoding (open) is applied in the first cycle, and encoding (deductive) is applied in the second cycle. For the qualitative data analyses, MAXQDA 12 software (VERBI GmbH, 2015) will be used.

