### Ethical considerations

3.7

This study was authorized by the regional ethics committee in April 2016 (Nr. PB_2016_00990), and data collection has started. The study will be executed in conformity with the Declaration of Helsinki (WMA, 2013) and with Good clinical practices (Altpeter et al., 2005).

The nurses and the nursing director will be asked for voluntary participation. Nursing records from the archives (pre‐intervention data) were permitted to be retrieved without patients’ informed consent. Written informed consent will be obtained for postintervention document analyses, for patient observations and for interviews. Comprehensive written and oral information on the study aim and procedures, together with descriptions of the patients’ rights as study participants, will be provided at least 1 day before data collection.

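### Record length has a four-day minimum but no common audit window or record-level adjustment, so diagnosis frequency and variety, a primary outcome, can be confounded by record length

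*Protocol article*

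**What the plan says.** All places are in the protocol article.

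- Nursing records (3.2.2): "Nursing records covering at least 4 days and at least one nursing diagnosis will be selected from all six wards". Fifteen records per ward are drawn before and fifteen after the intervention, so 45 per arm per period and 180 in all. No upper limit on length and no audit window is given.
- Expected outcomes (3.4): the primary outcomes include "the quality of nursing diagnoses, interventions and outcomes and the frequency and variety of NANDA‐I‐nursing diagnoses".
- Data analyses (3.6): diagnosis frequencies and patterns "will be compared between the two measurement time points and between the experimental and control groups". No denominator, test or length adjustment is named. For Q-DIO R, "scores will be summed for each sub‐concept" and unpaired t-tests follow if the data are normal.
- Tool for demographic and organizational data (3.5.1.7): "To control for system influences, the number of beds, capacity, patients’ length of stay" and other items are gathered for each ward. Section 3.6 uses organizational characteristics in correlations.
- Study design and setting (3.1): seven eligible wards (2 geriatric, 3 medical, 2 surgical). Three are drawn for each arm and one is left out, with no stratification by ward type stated.
- Ethical considerations (3.7): "Nursing records from the archives (pre‐intervention data) were permitted to be retrieved without patients’ informed consent", whereas written consent is needed for the post-intervention records.
- Patients (3.2.3): "From the randomly selected nursing records, four patients per ward will be included (*N = *24) to participate in interviews and clinical observations".

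**The concern.** The number of distinct diagnoses in a record cannot fall as the record runs on, and it can rise. A four-day surgical record and a much longer geriatric record both qualify, and the longer one has had more opportunity to accumulate diagnoses. Unequal length does no more than add noise while its distribution is the same in the groups compared. It biases the comparison when the distribution differs.

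The plan leaves two routes for that:

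- **Between arms.** Each arm is three wards of mixed specialty, too few for randomization to be relied on to balance length of stay.
- **Between periods.** Pre-intervention records come from the archive without consent. Post-intervention records need written consent, and some belong to patients who are observed and interviewed on the ward. The article does not say at what event a record is closed for audit.

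Either route could produce a difference in a primary outcome without any effect of GCR, or hide a real one. The data listed would not separate the two explanations, because length is not listed as a variable for each audited record.

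**Working it through.** **1. The plan's own figures.** The sample-size statement uses one-sided unpaired t-tests at 0.05. Solving the t-based power equation for effect sizes 0.63 (80%), 0.53 (80%) and 0.47 (70%) gives 31.9, 44.7 and 43.3 records per group. Rounded up these are 32, 45 and 44, as stated. They concern Q-DIO sub-concepts and are not in dispute. The article gives no planning figure for diagnosis frequency and no distribution of record length.

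**2. How often ward types balance.** Assumption: unstratified drawing, all draws equally likely.

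- All draws: C(7,3) × C(4,3) = 35 × 4 = 140.
- Same mix in both arms: the ward left out must be medical (3 ways), and each arm then has one ward of each type (2 × 2 × 2 = 8 ways). 3 × 8 = 24, and 24/140 = 17%.
- One arm has both geriatric wards, the other none: a non-geriatric ward is left out (5 ways) and both geriatric wards fall in the same arm (2 × 4 = 8 ways). 5 × 8 = 40, and 40/140 = 29%.
- Number of geriatric wards differs: those 40, plus draws in which a geriatric ward is left out (2 × C(6,3) = 40). 80/140 = 57%.

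This shows that unequal length between arms is plausible if stay differs by ward type. That condition is an assumption.

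**3. What a length gap could do to a count.** Every input here is assumed: 2 diagnoses by day 4, 0.1 to 0.3 new ones per further day, SD 1.5 to 2.0 per record, and a 4-day gap in mean length. Records are treated as independent.

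- Spurious difference d: 4 × 0.1 = 0.4 to 4 × 0.3 = 1.2 diagnoses per record.
- Rejection probability with 45 per group, when the longer records are in the experimental arm: 1 − Φ(1.645 − (d/SD) × √(45/2)).

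| d | SD 1.5 | SD 2.0 |
|---|---|---|
| 0.4 | 0.35 | 0.24 |
| 0.8 | 0.81 | 0.60 |
| 1.2 | 0.98 | 0.89 |

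- If the gap runs the other way, the sign before the shift changes. For d = 0.4 and SD 2.0 the result is 1 − Φ(1.645 + 0.949) = 0.005; for d = 1.2 and SD 1.5 it is practically 0. Wards are randomized, so both directions are equally likely. The averages are (0.24 + 0.005)/2 = 0.12 and (0.98 + 0)/2 = 0.49. In the unfavourable half, a real effect would tend to be hidden.

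**4. The same without an accrual model.** Let r be the correlation of length with the outcome and D the standardized length gap favouring the experimental arm. The spurious standardized effect is about r × D. With 45 per group, the one-sided rejection rate is 5.0% at r = 0 or D = 0. At D = 0.5 it is 12.0% for r = 0.2, 17.4% for r = 0.3 and 32.0% for r = 0.5.

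**5. How many post-intervention records are of patients seen on the ward.** 4 of 15 per ward, so 24 of 90 (27%), equally in both arms.

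**6. Which correction works.** Under the model in step 3, diagnoses per record-day are 2/4 = 0.50 at day 4, (2 + 0.4)/8 = 0.30 to (2 + 1.2)/8 = 0.40 at day 8, and (2 + 1.6)/20 = 0.18 to (2 + 4.8)/20 = 0.34 at day 20. A simple daily rate therefore depends on length too, in the opposite direction. A count over days 1-4 is 2 in every record whatever its length, so the spurious difference is 0.

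**The case against.** The strongest reply is that this is a condensed article. An audit window and a definition of the count may stand in a full protocol or audit manual that is not shown, and their absence alone would be no finding. That limits the point but does not remove it. The article gives a numerical length rule, names the level at which length of stay is collected and names the use made of organizational data. As fixed there, these do not protect a primary count outcome.

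A reader might infer three stronger things that the article does not support:

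- **That Q-DIO R scores measure length.** The items are bounded ratings (0-2 or 0-4), not tallies, and nothing in the article shows that they rise with length.
- **That whole records are audited and raw counts compared.** This would be reading a rule into silence. The article says neither this nor the opposite.
- **That post-intervention records are still open when audited.** A patient can be interviewed on the ward and the record audited after discharge.

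Two further replies carry some weight. The same six wards supply records in both periods, so stable ward differences would show at baseline and largely drop out of the pre/post comparison. The planned between-arm comparison after GCR, which the third hypothesis uses for Q-DIO R, remains exposed. Conversely, a shift between periods common to both arms cancels between arms but not in the pre/post comparisons. Each planned comparison thus remains open to one of the two routes. Lastly, length of stay is collected expressly to control for system influences, so the authors did not ignore it; but a ward-level correlation does not adjust the group comparison.

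**Conclusion.** The point stands for frequency and variety of NANDA-I diagnoses. A minimum length without a common window, and without a record-level length variable or adjustment, leaves this primary outcome open to confounding by record length in both planned comparisons. It becomes a bias only if length differs between the arms or between archived and consented records. Matching ward-type mixes in only 17% of unstratified draws make the first plausible, provided that stay differs by ward type. The second is a possibility that the article leaves open.

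The size of any bias cannot be computed from the article. The rejection rates of 24% to 98% are conditional on assumed accrual, SD and a 4-day gap that favours the experimental arm; they are not an expected error rate. For Q-DIO R an effect is possible but not shown. The stated sample sizes are unaffected. This is a cheap improvement, not a defect that invalidates the design.

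**What to change.** - Add a field for days covered to the SPSS data mask, fill it for each of the 180 records, and report it by arm and period.
- In 3.2.2 and 3.6, state that frequency and variety are compared over days 1-4, which every eligible record contains, alongside the full-record count.
- Analyse the full-record count with days covered as a covariate as a sensitivity analysis. Do not rely on a simple per-day rate.
- State the event at which a record is closed for audit, and use the same event in both periods.

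The cost is a sentence or two in each of the two sections and one extra field in records that are already being read. No further records or staff are needed. Data collection has started, but the dates can still be taken from the records. There are two downsides. Diagnoses first documented after day 4 appear only in the full-record analysis. Record length is also measured after allocation and could itself be affected by the intervention, so the adjusted result should be presented as a sensitivity check and not as the main estimate.

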## BACKGROUND

2

The nursing process provides a systematic approach for nursing care (American Nurses Association [ANA], 2015a). This relationship and problem‐solving process were further developed into an extended, deepened and research‐based version, so‐called Advanced Nursing Process. It “consists of defined, validated concepts. It includes assessment, nursing diagnoses, nursing interventions and nursing outcomes that are rooted in scientifically based nursing classifications” (Müller‐Staub et al., 2015, p. 13). Compared with the “traditional nursing process” without SNLs, the Advanced Nursing Process contains valid assessment tools and evidence‐based diagnoses, intervention and outcome concepts (=SNLs) as described in nursing classifications. The classification systems that best meet literature‐based validity and reliability criteria are the NANDA‐International Diagnoses Classification (NANDA‐I), the Nursing Outcomes Classification (NOC) and the Nursing Interventions Classification (NIC) (Odenbreit, Müller‐Staub, Brokel, Avant, & Keenan, 2013) (for abbreviations, see Table 1). These three classifications are linked and are referred to as the NANDA‐I, NIC and NOC (NNN) taxonomies (Johnson et al., 2011). The NNN taxonomies are recognized by the ANA (2015b) for their use in Electronic Health Records (as interface terminologies), as multidisciplinary reference terminologies in the Systematized Nomenclature of Medicine—Clinical Terms (SNOMED CT) and as well as Logical Observation Identifier Names and Codes (LOINC) for communicating similar meaning across different software systems and different settings. The application of the NNN taxonomy relies on clinical decision‐making including diagnostic, therapeutic and ethical judgements (Gordon, ; Müller‐Staub et al., 2015). After implementation of the Advanced Nursing Process, nurses stated more accurate nursing diagnoses and performed more effective interventions that led to better patient outcomes (Müller‐Staub, Needham, et al., 2008; Pérez Rivas et al., 2016). However, previous studies demonstrated deficits in the application of the Advanced Nursing Process, including severe documentation errors. Missing assessments, inaccurate nursing diagnoses and inconsistencies between diagnoses, interventions and outcomes have been reported (Gershater et al., 2010; Halvorsen, Eide, Sortland, & Almendingen, 2016; Kebede, Endris, & Zegeye, 2017; Paans, Sermeus, Nieweg, Krijnen, & Schans, 2012). For instance, only 36% of nursing diagnoses recognized by Registered Nurses (RNs) were documented in the nursing records (Kobleder, 2011). A considerable consequence of such deficiencies is impaired clinical decision‐making, which leads to less positive nursing‐sensitive outcomes (Paans, Sermeus, Nieweg, & Schans, 2010; Saranto & Kinnunen, 2009; Zegers et al., 2011). Gershater et al. (2010) also reported negative medical, professional and economic consequences. Many factors can lead to rudimentary applications of the Advanced Nursing Process*.* These factors were specifically identified in individuals (deficient nurse knowledge and attitude), in the social context (organizational culture and institutional structures) and in financial limitations (Grol & Wensing, 2013). Nurses need patient‐related knowledge in addition to knowledge regarding diagnostic concepts, evidence‐based interventions and outcomes (Lunney, 2010; Paans, Nieweg, van der Schans, & Sermeus, 2011). Nurses’ attitude towards the nursing process is seen as a major influencing factor on its application (Ajzen, 2012; Romero‐Sánchez, Paloma‐Castro, et al., 2013; Romero‐Sánchez, Paramio‐Cuevas, et al., 2013) and on diagnostic prevalence and accuracy (Collins, 2013; Paans et al., 2011). In addition, electronic and handwritten nursing records have been identified as obstacles: nursing diagnoses have been inaccurately documented, and nurses have been found to be unfamiliar with SNLs (Conrad, Hanson, Hasenau, & Stocker‐Schneider, 2012; Paans et al., 2012). With respect to organizational factors, the attitude of supervisors towards nursing diagnoses has been reported in previous studies as a significant influencing factor (Axelsson, Björvell, Mattiasson, & Randers, 2006; Westendorf, 2007) and also, organizational factors, such as staff turnover (particularly of nurse leaders), nurse–patient ratio, workload level and nursing organization systems, influence nurses’ diagnostic competencies and their performance of the nursing process (Paans et al., 2011).

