### Research questions

2.3

The main research question is What effect does GCR have on the Advanced Nursing Process? According to the operationalized levels of the Kirkpatrick model, the detailed research questions are
How do the participating nurses and the nursing director rate GCR? (Reaction)What effect does GCR have on nurses’ knowledge and on their attitude towards the Advanced Nursing Process in the learning field? (Learning)What effect does GCR have on nurses’ clinical performance and attitude towards the Advanced Nursing Process on the wards? How do patients describe their experience of the Advanced Nursing Process (nurses’ knowledge, skills and attitudes)? (Behaviour)What effect does CGR have on the accuracy of nursing diagnoses (including frequency and variety), the effectiveness of nursing interventions and the quality of nursing outcomes? (Results)Are the findings of data and method triangulation (satisfaction, knowledge, attitude, Q–DIO R scores, APNs and patients’ perspective on nurses’ clinical performance) mutually supportive to build a chain of evidence?

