### Study design and setting

3.1

A complex experimental intervention study using data and method triangulation will be performed. A complex intervention contains a “number of interacting components […], number and difficulty of behaviours required by those delivering or receiving the intervention, number of groups or organizational levels targeted by the intervention, number and variability of outcomes [and] degree of flexibility or tailoring of the intervention permitted” (Craig et al., 2008). General teaching and learning processes as well as GCR are guided and influenced by teachers’ and participants’ behaviour and various context conditions. Furthermore, the knowledge transfer from the learning field to the work field including organizational influencing factors will be considered, and therefore, several outcomes on different levels will be measured. Quantitative methods will be used to take knowledge tests and self‐assessments on nurses’ attitude towards the Advanced Nursing Process. The quality of the Advanced Nursing Process—including the accuracy, frequency and variety of nursing diagnoses—will be evaluated by nursing record audits with the Q‐DIO R instrument. However, a general criticism is how the nursing reality is represented in the nursing records. Therefore, to the objectives of level 3 evaluation, observations of nurses’ clinical performance of the Advanced Nursing Process, interviews with patients and qualitative document analyses will be performed to verify the Q‐DIO results (Kirkpatrick & Kirkpatrick, 2008, 2010).

The study will be conducted in a Swiss public hospital. From a total of 12 wards, seven fulfil the inclusion criteria in that they are acute geriatric (2), internal medicine (3) or surgical (2) inpatient wards. By sealed‐envelope drawings, three wards will be randomly allocated to the experimental group, three to the control group and one will be excluded.

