### Study intervention

3.3

Guided clinical reasoning will be applied to the experimental group on GCR training days. The intervention comprises four single days at a duration of 5 months, and each GCR day comprises 7 hr. The participating nurses will receive materials on the Advanced Nursing Process including presentations, information about relevant websites, assigned reading and work assignments (Table 2). These documents will be distributed in printed form or as PDF files. Prior to starting GCR, the participating nurses will be asked about their previous knowledge, experiences, learning needs and interests. On each of the four GCR training days, several learning methods will be applied such as a GCR case‐meeting, presentations, small‐group work and discussion rounds. Additional work assignments (transfer tasks) to put the newly gained knowledge into clinical practice include formulating and documenting SNL‐based, accurate nursing diagnoses for a patient in the PES format (problem definition, aetiological factors and signs/symptoms) and writing coherent care plans. Verifying nursing diagnoses and the care plan with the patient is strongly recommended.

**Table 2 nop2299-tbl-0002:** Standardized educational intervention protocol GCR

Date	Objectives/contents	Assigned reading
Day 1	Advanced Nursing Process and nursing diagnoses (objectives, purpose, advantages and disadvantages, terms/definitions/concepts, references to nursing science, historical background, prospects, frequent nursing diagnoses, components of nursing diagnoses—PES format) Diagnostic process (steps, exercises, difficulties) NANDA‐I Taxonomy II (application of the work by Doenges et al. (2014)	History of the nursing process Clinical decision‐making in the diagnostic process by means of case‐meeting GCR Nursing process for leaders
Day 2	Reflections on assigned readings and examination of work assignments Exploration/definition of concepts (e.g. Advanced Nursing Process and nursing diagnostics) Problem areas in practical implementation Repetition of nursing diagnostic steps and clinical decision‐making Historical background and prospects NANDA‐I Taxonomy II (application of the work by Doenges et al. (2014)	Quality improvement by nursing diagnoses? Systematic review: nursing diagnoses, interventions and outcomes—application and impact on nursing practice Evaluation study relating to the implementation of nursing diagnoses, interventions and outcomes

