#### Measurement time points before and after the GCR study intervention

3.5.2

Data collection will occur at three time points; the flow chart in Figure 3 presents all data collection methods and time points. As baseline measurement before the GCR intervention (*t*0_1_ + *t*0_2, _illustrated in boxes): a sample of nursing records will be drawn, and nurses of the intervention and control group perform the knowledge tests and all nurses of the participating wards fill out the PND scales (illustrated in circles). After GCR, the participants complete knowledge tests and PNDs for the second time and complete the satisfaction survey (*t*1). After ending of the GCR intervention, all nurses complete the PND a second and a third time. At that time, a second sample of nursing records will be drawn. In addition, patient care will be observed (nurses’ clinical performance) and patients are interviewed to cross‐validate the Q‐DIO R results on the quality of the Advanced Nursing Process as described in the nursing records.

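### Records enter the audit only if they hold at least one nursing diagnosis, so the primary frequency outcome is cut off at 1 and post-intervention records are selected on something GCR can change

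*Protocol article*

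**What the plan says.** The record sample is defined in section 3.2.2: "Nursing records covering at least 4 days and at least one nursing diagnosis will be selected from all six wards". The same rule covers both arms and both periods, with 15 records per ward and period. Wards are the allocated units: "three wards will be randomly allocated to the experimental group, three to the control group and one will be excluded" (section 3.1). After the intervention, "At that time, a second sample of nursing records will be drawn" (section 3.5.2).

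Section 3.4 lists among the primary outcomes "the quality of nursing diagnoses, interventions and outcomes and the frequency and variety of" NANDA-I diagnoses, and the Results-level question in section 2.3 repeats frequency and variety. Section 3.6 says that the frequencies and patterns "will be compared between the two measurement time points and between the experimental and control groups". The training itself works on documentation: its transfer tasks have nurses write up "accurate nursing diagnoses for a patient in the PES format" (section 3.3).

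The article does not mention counting the records that are passed over because they hold no diagnosis.

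**The concern.** Whether a post-intervention record qualifies depends on what nurses wrote after their ward was allocated and trained. Writing diagnoses is what GCR teaches. Two things follow from the text without any numerical assumption.

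- A record's diagnosis count starts at 1. If GCR turns a record with no diagnosis into a record with one, the primary frequency outcome cannot register that gain.
- If GCR raises the share of records with a diagnosis, the experimental wards contribute kinds of record that stay excluded on the control wards. The post-intervention arms are then no longer like-for-like samples of stays.

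At stake is an understated frequency effect, and a quality comparison that describes only records with a diagnosis while being read as describing all records.

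**Working it through.** **The plan's own figures.** Section 3.2.2 gives 32, 45 and 44 records per group for diagnoses, interventions and outcomes (effect sizes 0.63, 0.53 and 0.47; power 80%, 80% and 70%; one-sided 0.05). An unpaired t-test calculation gives 31.9, 44.7 and 43.3, which round up to 32, 45 and 44. The sample-size arithmetic reproduces and is not in question.

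**Records affected.** 3 wards × 15 records = 45 per arm and period. Two arms give 90 post-intervention records, which GCR can have selected, and 90 baseline records, which are truncated but which GCR cannot have influenced.

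**Frequency.** The share of stays without a diagnosis is not in the article, so a range is needed. Assume that the count per record is Poisson with mean λ. Then the share excluded is exp(−λ), and the mean among admitted records is λ / (1 − exp(−λ)). For λ = 1: 1 / (1 − 0.368) = 1.582. For λ = 2: 2 / (1 − 0.135) = 2.313. The visible difference is 0.731 against a true 1.

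| True means, control v GCR | Excluded, control v GCR | Means after truncation | True difference | Visible difference | Lost |
|---|---|---|---|---|---|
| 0.5 v 1 | 61% v 37% | 1.271 v 1.582 | 0.5 | 0.311 | 38% |
| 1 v 2 | 37% v 14% | 1.582 v 2.313 | 1 | 0.731 | 27% |
| 2 v 3 | 14% v 5% | 2.313 v 3.157 | 1 | 0.844 | 16% |
| 3 v 4 | 5% v 2% | 3.157 v 4.075 | 1 | 0.917 | 8% |
| 4 v 5 | 2% v 1% | 4.075 v 5.034 | 1 | 0.959 | 4% |

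**Quality.** Suppose that GCR truly adds 0.5 points on the 0–4 scale (the raw effect in section 3.2.2), raises the share of records with a diagnosis from p0 to p1, and that the newly eligible records score g points below the others. The difference seen among eligible records is 0.5 − g × (p1 − p0) / p1.

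- From 70% to 90%: (0.9 − 0.7) / 0.9 = 0.222. For g = 0, 0.5 and 1.0 the visible difference is 0.50, 0.39 and 0.28.
- From 90% to 100%: (1.0 − 0.9) / 1.0 = 0.10. The same values of g give 0.50, 0.45 and 0.40.
- If newly eligible records scored higher instead (g = −0.5, 70% to 90%): 0.5 + 0.111 = 0.61.
- If p1 = p0, the second term is 0 and there is no bias.

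So the sign depends on which records become eligible, and the article gives no information on that.

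**The case against.** **The loss may be small.** Control wards continue a nursing process that already includes NANDA-I diagnoses (section 3.3), and the nurses are included because they apply the Advanced Nursing Process (section 3.2.1). If almost every stay of 4 days or more carries a diagnosis, the lower rows of the table apply. This stands. But the rule as written leaves the share unknown.

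**The Background does not show many empty records.** A reader might infer from "only 36% of nursing diagnoses recognized by Registered Nurses (RNs) were documented in the nursing records" that missing diagnoses are the main deficit and that many records hold none. Section 2 does not support this. The figure is one example beside missing assessments, inaccurate diagnoses and inconsistent care plans, and it is a share of recognised diagnoses, not of records. If 5 diagnoses were recognised per patient and documented independently, 0.64^5 = 11% of records would be empty; with 8, 0.64^8 = 3%. Both the counts and the independence are assumptions.

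**The rule may exist so that the Q-DIO R diagnosis items can be scored.** That is a fair reason for a conditional quality analysis. It is no reason to truncate frequency.

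**A stronger claim about quality is tempting.** One could score absent diagnoses as 0 and, with 37% v 14% excluded and a mean of 2.0 in both arms, say that (0.368 − 0.135) × 2.0 = 0.47 points are hidden, nearly all of the assumed 0.5. The article does not say that absence scores 0. The 0.47 mixes presence with quality, so it estimates something other than the quality of documented diagnoses and should not be set against the 0.5.

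**No false-positive mechanism is shown.** If GCR has no effect, it does not change eligibility and creates no differential selection. This stands.

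**Frequency is not defined as a mean count per record.** It could mean how often each diagnosis label occurs. The table's percentages apply only to the count reading. If label frequency is expressed per record, the denominator still omits empty records; if it is a share of all diagnoses, empty records contribute nothing and truncation does not matter.

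**Conclusion.** The point holds for the frequency outcome: as a count per record it is truncated at 1 in both periods, and the 90 post-intervention records are chosen on a variable that GCR is meant to affect. This is a stated eligibility rule, not a detail that the article leaves out, and later analysis cannot restore records that were neither drawn nor counted.

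The size is not known from the article. Under Poisson counts the loss runs from about 4% to 38% of the true difference in means over the cases shown, and it is small where nearly every record has a diagnosis. For the Q-DIO R scores the supported conclusion is narrower: the comparison is conditional on a diagnosis being present, and any bias needs GCR to change eligibility and could go either way. The documents do not support saying that the rule hides most of the quality effect, or that it favours GCR when GCR does nothing.

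**What to change.** - **Draw.** Sample at random from all stays of at least 4 days until 15 records with a diagnosis are reached per ward and period, and log every drawn record that has none.
- **Frequency.** Count the logged records as zero. Report the proportion with at least one diagnosis by arm and period. Because drawing stops at the 15th record with a diagnosis, the simple share 15/N among N drawn is slightly high; (15 − 1)/(N − 1) corrects it (for N = 20, 0.737 instead of 0.750).
- **Quality.** Keep the Q-DIO R scores on the 15 records with a diagnosis and label that comparison as conditional on a documented diagnosis.
- **Baseline.** Section 3.7 says that data collection has started. For baseline records already drawn, recover from the archive the number rejected per ward. No redraw or re-audit is needed, so the quality samples keep the same rule before and after.

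The cost is a small tally and a more skewed frequency distribution. Section 3.7 requires written consent for post-intervention document analysis, so check whether logging a post-intervention record without a diagnosis falls under that consent.
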